#### Follow up assessment at 3 and 6 months

A site research assistant will arrange a follow-up assessment for any participants deemed at their previous visit not to be fully recovered (HB score greater than 1). For participants unable to attend the study site, assessment will be conducted remotely as previously described.

Participants deemed to have fully recovered at the 1 month visit will not be required to attend the study site for the remaining study time points; the parent/guardian or participants (age dependent) will instead be asked to complete the questionnaires online or via mail (or via telephone, administered by the research assistant if required). The questionnaires will be the same as those completed by the unrecovered participants but without HB, Sunnybrook, SAQ scoring or facial imaging. Similarly, participants who have fully recovered at the 3 month visit will not be required to attend the study site for the 6 month time point and the parent/guardian/participant will instead be asked to complete the questionnaires online or via mail (or via telephone, administered by the research assistant if required).

Parent/guardian or participant questionnaires, grading scales and facial imaging will be performed similar to the 1 month visit (see Table 1).

#### Follow up assessment at 12 months

For participants not recovered at 6 months, a further contact will be conducted with the parent/guardian or participant with a request to complete a questionnaire on-line or by phone to elicit information on parent perceived recovery of Bell’s palsy. While this data point is outside the RCT period of 6 months, this will allow the determination of the 12 month recovery rate for Bell’s palsy in children which is unknown at this time.

### Statistical methods

#### Sample size estimation

Based on observational data [4, 14] we expect 60 % of children without prednisolone to have complete recovery at 1 month. This is in line with data from the pediatric RCT which reported complete recovery without prednisolone in 72 % at 4 months [12]. A study in adults [18] deemed an improvement of 12 % with prednisolone compared with placebo to be a clinically important difference between treatment groups. We therefore power our study to find an increase in the proportion with complete recovery from 60 % in the placebo group to 72 % in the prednisolone group. This is a conservative estimate of efficacy compared with that found in our observational pilot data [4, 14] which showed an increase in complete recovery at 1 month of 16 % in those treated with prednisolone (75 %) compared with those not receiving prednisolone (59 %). To enable us to identify an increase in recovery from 60 to 72 % or larger with 80 % power requires a study with 244 subjects in each treatment group based on a two-sided test with α = 0.05. Hence we aim to recruit 270 per group (540 in total) to allow for 10 % loss to follow-up at 1 month.

#### Statistical analysis

Data will be analysed on an intention-to-treat basis. For the primary analysis, multiple imputation will be used to handle missing data, imputing all outcomes using a single (joint) imputation model. Imputation will be carried out separately by treatment arm to ensure that any treatment effects are maintained. As a secondary analysis, all analyses will be repeated using a complete case analysis, including all participants with data available for each outcome.

The primary outcome of complete recovery at 1 month post randomization on the HB scale (as determined by the site specialist clinician) will be presented as a proportion in each treatment group, with a comparison between the groups presented as a difference in proportions and as an odds ratio from a logistic regression model adjusted for site and age, with a 95 % CI and *p*-value. In addition, we will present the results as Number-Needed-to-Treat (NNT) and its 95 % CI. As an additional sensitivity analysis, the analysis of recovery at 1 month will be repeated assuming that all participants with missing data who have not previously been recorded as achieving complete recovery 1) have recovered, and 2) have not recovered.

All secondary outcomes will be summarized by treatment group. Binary outcomes will be presented as proportions, with comparisons between the groups presented as a difference in proportions and as odds ratios from logistic regression adjusted for site, with 95 % CIs and *p*-values. Continuous outcomes will be presented as means and standard deviations, with comparisons made using linear regression adjusted for site presented as mean differences, 95 % CIs and *p*-values. Time to recovery will be assessed using a Cox proportional hazards model censoring patients who have not recovered at 6 months, with results presented as a hazard ratio, and its 95 % CI and *p*-value. Participants who have reached complete recovery at 1 or 3 months and are not assessed at the later time points will be assumed to have complete recovery for the duration of the study. For both the primary and secondary outcome, we will repeat the analysis adjusted for age (as a continuous variable), gender, baseline severity of facial nerve dysfunction (severe = HB V and VI, non severe = HB I-IV [18, [36]) and time to treatment (≥24 vs >24–72 hours [18, [36]) as potentially important confounders.

Whether the effectiveness of the intervention in improving the proportion recovered at 1, 3 and 6 months varies according to age, time to treatment and initial severity will be assessed by the addition of an interaction between treatment and the covariate to the logistic regression model.

Face-to-face and video HB scores and the HB vs Sunnybrook scoring will be compared using scatterplots and kappa statistics.

Finally, the effect of prednisolone compared with placebo on health economic markers will be assessed using decision analysis using a comparison of the 6 month treatment cost data and results from the CHU9D administered at 1 month, 3 months and 6 month.

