## Methods

### Study design

This is a phase III, triple-blinded, randomised, placebo-controlled superiority trial of prednisolone for treatment of Bell’s palsy. Participants will be randomised in a 1:1 ratio to receive ~ 1 mg/kg/day of prednisolone, up to a maximum of 50 mg, or matched placebo for 10 days. The study will include a total of 540 children (approximately 270 in each treatment group). This sample size allows for 10 % loss to follow-up at 1 month. The study will be conducted at sites of the Paediatric Research in Emergency Departments International Collaborative (PREDICT) research network in Australia and New Zealand [28]. The central study site is the Murdoch Childrens Research Institute in Melbourne (MCRI), Australia and the central study pharmacy is at the co-located Royal Children’s Hospital (RCH), Melbourne, Australia.

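### Complete-case recovery at 3 and 6 months is overstated in both arms, because recorded recoveries always count as data and unrecovered children count only if seen

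*Protocol article*

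**What the plan says.** Three rules in the protocol article bear on HB recovery at 3 and 6 months, which are named secondary outcomes.

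- **Complete case.** Under Statistical analysis, the main approach is joint multiple imputation by arm. All analyses are then repeated "using a complete case analysis, including all participants with data available for each outcome".
- **Carry-forward.** The same section has a rule for a recovery recorded at month 1 or month 3: such children who "are not assessed at the later time points will be assumed to have complete recovery for the duration of the study".
- **Who is scored.** Under Follow up assessment at 3 and 6 months, "Participants deemed to have fully recovered at the 1 month visit will not be required to attend the study site"; they complete questionnaires only. A visit is arranged for "any participants deemed at their previous visit not to be fully recovered (HB score greater than 1"). Footnote b of Table 2 agrees.

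The analysis that sets missing outcomes to all recovered and then to all not recovered is stated for 1 month only.

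**The concern.** Put together, the rules make inclusion in the complete-case set depend on the outcome. A recorded recovery supplies an HB result for every later visit without the child being seen. A child not recorded as recovered supplies one only by being assessed. The denominator keeps all earlier recorded recoveries and loses some of the unrecovered. Informative drop-out is not needed: visits missed purely at random among those due are enough.

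Reading data availability as excluding carried-forward results does not help. The analysis would then contain almost only children who were unrecovered at their previous visit.

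At 3 and 6 months the complete-case result is the only stated check on the imputation. A sound imputation would disagree with it for a mechanical reason, and a reader could take the gap as a sign that the results are sensitive to missing data.

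**Working it through.** **Inputs from the protocol article**
- Recovery at 1 month "from 60 % in the placebo group to 72 % in the prednisolone group", so the unrecovered share u is 0.40 v 0.28 (Sample size estimation).
- Allocation 1:1 (Study design).
- An allowance of 10% for "loss to follow-up at 1 month". No figure is given for 3 or 6 months.

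**Assumptions, not in the document**
- A share q = 0.5 of the unrecovered recover by each next visit, in both arms.
- A share m = 10%, 20% or 30% of due visits is missed at random, equally in both arms.

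**The plan's own figure.** The plan "requires a study with 244 subjects in each treatment group based on a two-sided test with α = 0.05". With pooled variance and no continuity correction, n = [1.960·√(2×0.66×0.34) + 0.842·√(0.60×0.40 + 0.72×0.28)]² / 0.12² = 243.4, rounded up to 244. It reproduces, so the design rates are a fair starting point.

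**Three months.** Let p = 1 − u.
- True non-recovery = u(1 − q).
- Complete-case non-recovery = u(1 − q)(1 − m) / (1 − mu), because only the unrecovered can drop out.
- The factor g = (1 − m)/(1 − mu) is below 1 whenever some due visits are missed and some children had recovered. Recovery is therefore overstated in each arm.
- Example, m = 10%: placebo 0.20 × 0.9/0.96 = 0.1875; prednisolone 0.14 × 0.9/0.972 = 0.1296.

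| Due visits missed | Placebo | Prednisolone | Difference (points) | Odds ratio |
|---|---|---|---|---|
| None (truth) | 80.0% | 86.0% | 6.0 | 1.54 |
| 10% | 81.3% | 87.0% | 5.8 | 1.55 |
| 20% | 82.6% | 88.1% | 5.5 | 1.56 |
| 30% | 84.1% | 89.3% | 5.2 | 1.58 |

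The ratio of complete-case to true difference is (1 − m)/[(1 − 0.40m)(1 − 0.28m)] = 0.965, 0.921 and 0.868, whatever the common q. If 10% are also missed at random at 1 month, simulation changes little: at m = 20% it gives 82.4% v 88.0%.

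**Six months** (true 90% v 93%, difference 3.0 points). The result depends on what happens to a child who misses month 3.
- *May return at month 6.* Non-recovery = u(1 − q)²(1 − m) / {p + uq(1 − m) + [u(1 − q) + uqm](1 − m)}. At m = 30%: 0.070/0.922 = 7.6% v 0.049/0.9454 = 5.2%. Differences for m = 10%, 20%, 30% are 2.8, 2.6 and 2.4 points.
- *Lost for good.* Non-recovery = u(1 − q)²(1 − m)² / [p + uq(1 − m) + u(1 − q)(1 − m)²]. At m = 30%: 0.049/0.838 = 5.8% v 0.0343/0.8866 = 3.9%. Differences are 2.7, 2.3 and 2.0 points.

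**When the difference does not shrink.** It shrinks only if true non-recovery in placebo divided by that in prednisolone exceeds (1 − g for prednisolone)/(1 − g for placebo), which is about 1.19, 1.17 and 1.15 for the three values of m. Here the ratio is 0.20/0.14 = 1.43. If placebo catches up to 85% v 85%, complete case produces a false difference of +0.2, +0.3 and +0.5 points. At m = 30%, for instance, non-recovery is 0.15 × 0.7/0.88 = 11.9% v 0.15 × 0.7/0.916 = 11.5%.

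**The case against.** The strongest reply is that the main analysis already covers this. Joint imputation of all outcomes by arm can use earlier recovery status, and visits missed at random given that status are the case it handles. Complete case is labelled secondary, and these are secondary outcomes. That stands, and it is why the point is minor. It does not remove the point, because the biased result would still be reported as the check.

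Second, the error is small against sampling noise. At 20% missed, the 3-month difference moves by 0.5 points, while its simulated standard deviation is about 3.3 points for complete case and 3.7 for the stepwise estimate. For the treatment difference alone, the remedy therefore gives up a little precision to remove a small bias. That also stands. The gain is in the recovery levels and in a check that does not diverge for an artificial reason.

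Third, this could be called detail for the statistical analysis plan. Both rules, however, are stated in the article, and the conflict comes from what they say.

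Some stronger readings are tempting and not supported:
- *The treatment effect is biased toward no effect.* The plan reports a difference in proportions and an odds ratio. On these assumptions the first shrinks and the second rises. The first also reverses if placebo nearly catches up, which is plausible given the Background statement that up to 100% of children recover within 12 months.
- *Recovered children are never missing.* This holds only for recorded recovery. A child who recovers between visits and misses the next one is missing.
- *The 6-month difference loses a third.* This needs 30% of due visits missed and every child who misses month 3 lost for good. Nothing in the visit schedule removes such a child from month 6. If the child may return, the loss is about a fifth (3.0 to 2.4).

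**Conclusion.** The concern holds in a limited form. As written, complete-case HB recovery at 3 and 6 months overstates recovery in both arms whenever due visits are missed, even at random. On the stated assumptions the overstatement at 3 months is about 1 to 4 points. The 3-month difference loses 0.2 to 0.8 of 6.0 points, and the odds ratio rises by up to about 0.04. At 6 months the 3.0-point difference becomes 2.8 to 2.4 if children may return after a missed visit, or 2.7 to 2.0 if they do not. Later recovery and missed-visit rates are assumptions, since the document gives none. The direction of bias in the treatment effect is not fixed. The 1-month primary outcome is untouched, and so is the imputation if its joint model includes earlier recovery status. Severity is minor.

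**What to change.** For HB recovery at 3 and 6 months:

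1. State that conclusions rest on the multiple imputation, and that its model includes recovery status at earlier visits.
2. Replace the plain complete-case proportion with a stepwise estimate in each arm: the proportion recovered at 1 month, plus the proportion not recovered times the proportion recovering by 3 months among those due and seen, and likewise to 6 months. Alternatively, weight each due child who is seen by the inverse of that arm's attendance among those due. Use a bootstrap or robust confidence interval.
3. Report the numbers due and the numbers seen, by arm and visit.

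The stepwise estimate recovers the true levels in simulation (80.1% v 86.0% at 3 months and 90.0% v 93.0% at 6 months, with 80% attendance). It rests on much the same missing-at-random assumption as the imputation, so it serves as a consistency check and does not test that assumption. The cost is some wording, a small amount of analysis and a modestly wider interval (standard deviation of the 3-month difference about 3.7 against 3.3 points). Visits and data collection do not change.

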#### Baseline assessment and randomisation during the ED visit

Following informed consent, eligibility check and randomisation, demographics and relevant clinical information will be collected from the patient including side of the palsy, onset and associated symptoms, relevant past medical history, and medical evaluations/contacts prior to the ED visit.

Study assessments regarding the severity of facial palsy as measured by the HB and Sunnybrook scales and facial imaging (digital video recording and still photographs) will be conducted using standardized instructions based on the study by Sullivan et al. [36]. A camera will be provided to all study sites. The images will be assessed at a later time point by assessors blinded to the study treatment assignment for quality control purposes.

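### Baseline palsy severity, scored on Day 1, is left out of the primary model; adding it in graded form would gain some efficiency at almost no cost

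*Protocol article*

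**What the plan says.** The Statistical analysis section states that the primary outcome will be "presented as a difference in proportions and as an odds ratio from a logistic regression model adjusted for site and age". The Abstract names the same two covariates. Binary secondary outcomes, which include HB recovery at 3 and 6 months, are adjusted for site.

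Severity is measured before any treatment effect can occur. The section on the baseline assessment in the emergency department provides for "Study assessments regarding the severity of facial palsy as measured by the HB and Sunnybrook scales", and Table 2 schedules both scales on Day 1.

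Severity appears in the analysis in two places. One is a repeat analysis of the primary and secondary outcomes that adds age, gender, time to treatment and "baseline severity of facial nerve dysfunction (severe = HB V and VI, non severe = HB I-IV"), which the plan regards as possible confounders of some importance. The other is a treatment-by-severity interaction test.

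The sample size is set to detect an increase "from 60 % in the placebo group to 72 % in the prednisolone group", and "with 80 % power requires a study with 244 subjects in each treatment group", "based on a two-sided test with α = 0.05".

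**The concern.** The primary outcome is HB grade 1 at 1 month, so baseline HB is the starting value of the outcome scale itself and an obvious candidate covariate. The plan gives no reason for putting age in the headline model and leaving severity to a repeat. In the repeat, the two-group split treats a child at HB II the same as one at HB IV.

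If severity predicts recovery, a primary model without it has less power than the same data could give, and a wider interval for the risk difference than a standardised estimate would have. The sample size was set at 80% power, so even a few points would be useful.

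**Working it through.** **Inputs from the Protocol article.** Recovery 0.60 and 0.72; two-sided α = 0.05; 80% power; 244 per group; 1:1 allocation; 270 per group recruited "to allow for 10 % loss to follow-up at 1 month".

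**Input not in the document.** How strongly baseline severity predicts recovery at 1 month. The Background lists the effect of initial severity among the questions the trial will inform. The ranges below are assumptions and include the case of no effect.

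**Step 1: reproduce the plan's figure.** With pooled variance under the null and no continuity correction, n = [1.960·√(2·0.66·0.34) + 0.842·√(0.60·0.40 + 0.72·0.28)]² / 0.12² = (1.313 + 0.559)² / 0.0144 ≈ 243.4, so 244. This agrees. Power at 244 per group is 80.1%. With 10% lost from 270, 243 remain and power is 79.9%.

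**Step 2: variance-factor approximation.** If severity explains a share R² of outcome variance, the effective n per group is 244/(1 − R²).

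| R² | effective n per group | power | n per group for 80% | CI width ratio √(1 − R²) |
|---|---|---|---|---|
| 0 | 244.0 | 80.1% | 244 | 1.000 |
| 0.05 | 256.8 | 82.1% | 232 | 0.975 |
| 0.10 | 271.1 | 84.1% | 220 | 0.949 |
| 0.15 | 287.1 | 86.1% | 208 | 0.922 |

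**Step 3: simulation, severity in two groups.** 244 per group, marginal rates 0.60 and 0.72, logistic model without and with severity, 30% of children severe, 4,000 runs per row. Site and age were not simulated. The gap is how much lower recovery is in severe children in the placebo group.

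| gap (points) | R² | power without | power with |
|---|---|---|---|
| 0 | 0.000 | 80.9% | 80.6% |
| 10 | 0.009 | 80.0% | 80.1% |
| 20 | 0.035 | 80.8% | 82.3% |
| 30 | 0.079 | 80.7% | 83.4% |
| 40 | 0.140 | 80.0% | 85.9% |

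With 20% or 50% severe, the 40-point gap gives 80.0% to 83.9% and 79.5% to 85.7%.

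**Step 4: simulation, graded severity.** Normal score, two-group version cut at 30% severe, 3,000 runs per row.

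| odds ratio per SD | none | two groups | graded |
|---|---|---|---|
| 1.28 | 81.0% | 80.8% | 80.8% |
| 1.65 | 79.7% | 81.2% | 81.6% |
| 2.12 | 80.1% | 83.2% | 85.0% |
| 2.72 | 80.0% | 83.5% | 85.9% |

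A separate set of 1,500 runs per setting, with graded severity at R² 0.05, 0.11 and 0.15, gave 81.9%, 84.7% and 87.4%, against 79.7% to 81.1% unadjusted. Simulation error on one power figure is about √(0.8·0.2/3000) = 0.7 points at 3,000 runs. Measured from 80.1%, the gain is 82.1 − 80.1 = 2.0 points at R² 0.05. At R² 0.15 it is 86.1 − 80.1 = 6.0 (approximation) to 87.4 − 80.1 = 7.3 (simulation).

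**Step 5: where precision improves.** At the 40-point gap with 30% severe, the standard error of the risk difference falls from 0.0423 to 0.0399 (0.0399/0.0423 = 0.943, about 6% smaller). The standard error of the log odds ratio rises from 0.194 to 0.211, while the odds ratio moves from 1.71 to a conditional 1.87. The ratio of effect to standard error goes from ln 1.71/0.194 ≈ 2.77 to ln 1.87/0.211 ≈ 2.97. Power therefore rises because the conditional effect is larger, not because its standard error is smaller.

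**The case against.** The strongest reply is that nothing here is wrong. Site, the stratification factor, is in the primary model. It is clear which analysis is primary. A severity-adjusted repeat is pre-specified for primary and secondary outcomes alike. All of that stands. It makes this an improvement to a valid plan, but it does not explain why the better-informed model is the secondary one.

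Several stronger readings are tempting, and the document does not support them:

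- *The trial is underpowered or the primary estimate is biased.* Step 1 shows that the 80% target is met without severity, and 79.9% after loss is rounding. A difference in severity between randomised groups arises by chance.
- *Severity is a strong predictor.* No figure is given. With a gap of 0 to 10 points the gain is nil within simulation error.
- *Adjustment sharpens the odds ratio.* Step 5 shows the opposite on the log scale.
- *The two-group split discards a known share of information.* For a normal score, a split retains about 34% at 90/10, 49% at 80/20 and 64% at 50/50. HB is a short ordinal grade and its baseline distribution is not given, so none of these can be assigned to this trial. In Step 4, grading adds at most about 2.4 points over the split (83.5% to 85.9%).
- *The difference in proportions is not adjusted at all.* The condensed sentence can be read either way, and how the difference is computed is a detail for the full analysis plan.
- *Recovery at 1, 3 and 6 months cannot be compared.* The headline covariates do differ, but the repeat analysis adds one common list at every visit.

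It is also fair to say that keeping the site-and-age model as a sensitivity analysis still leaves two adjusted results. The change reverses their order; it does not remove one.

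**Conclusion.** The point holds as forgone efficiency. The headline model omits a collected baseline measure of the outcome scale, and the repeat analysis uses it in coarse form. The gain from including it in graded form is about 0 points of power if it is not prognostic, and roughly 2 to 7 points if it explains 5% to 15% of outcome variance. At R² 0.10, 220 per group would give the power that now takes 244. These sizes rest on an assumed prognostic strength and on simulations without site or age. The direction does not depend on the exact value chosen, and the cost if severity proves uninformative is negligible (80.9% against 80.6%, within simulation error). It is a sensible change to make, not a condition of the trial's validity.

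**What to change.** Before unblinding, pre-specify the primary model as a logistic regression on treatment, site, age (continuous) and baseline severity in graded form, using either HB grade as an ordered score or Sunnybrook as a continuous score. Name one of the two in advance. Derive the risk difference, its 95% CI and the NNT from that model by marginal standardisation. Use the same covariates for recovery at 3 and 6 months. Keep the site-and-age model as a sensitivity analysis.

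Report the odds ratio as conditional on severity, and state that its log-scale standard error is expected to be larger than in the site-and-age model; the precision gain should be read from the standardised risk difference.

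The cost is a dated change of wording in the analysis plan. No extra data, visits or participants are needed.

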**Methods/Design:**

We are conducting a randomised, triple-blinded, placebo controlled trial of the use of prednisolone to improve recovery from Bell’s palsy at 1 month. Study sites are 10 hospitals within the Australian and New Zealand PREDICT (Paediatric Research in Emergency Departments International Collaborative) research network. 540 participants will be enrolled. To be eligible patients need to be aged 6 months to < 18 years and present within 72 hours of onset of clinician diagnosed Bell’s palsy to one of the participating hospital emergency departments. Patients will be excluded in case of current use of or contraindications to steroids or if there is an alternative diagnosis. Participants will receive either prednisolone 1 mg/kg/day to a maximum of 50 mg/day or taste matched placebo for 10 days. The primary outcome is complete recovery by House-Brackmann scale at 1 month. Secondary outcomes include assessment of recovery using the Sunnybrook scale, the emotional and functional wellbeing of the participants using the Pediatric Quality of Life Inventory and Child Health Utility 9D Scale, pain using Faces Pain Scale Revised or visual analogue scales, synkinesis using a synkinesis assessment questionnaire and health utilisation costs at 1, 3 and 6 months. Participants will be tracked to 12 months if not recovered earlier. Data analysis will be by intention to treat with primary outcome presented as differences in proportions and an odds ratio adjusted for site and age.

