### Randomisation

Participants will be randomized in a 1:1 ratio to one of two treatment arms: intervention (prednisolone) or matched placebo. An independent statistician has generated a randomization schedule using variable block sizes, stratified by site. This schedule will be used by the central study pharmacist at RCH to undertake the blinding, labelling and distribution of the study drugs to participating sites by putting together study packs of the required drug labelled with sequential study numbers for each site and dosing instructions. Randomization will be undertaken at the site by ED and research staff by selecting the lowest numbered study pack (next pack system) from the study drug store in ED.

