#### Interim analysis and stopping rules

The study will be monitored by an independent Data and Safety Monitoring Board (DSMB). A single interim analysis of the primary outcome will be undertaken and reported to the DSMB after 50 % of participants have completed the 1 month assessment (i.e. primary outcome data available for 244 participants). The Haybittle-Peto rule [51] will be used as a guideline for the DSMB, where the DSMB may recommend the trial be stopped if the level of significance of 0.001 is reached.

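### The site and age adjustment is tied only to the odds ratio, so the primary difference in proportions and the NNT appear to be unadjusted, and no p-value is named as deciding

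*Protocol article*

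**What the plan says.** The Statistical analysis section gives the primary outcome, complete recovery at 1 month, as a proportion per arm. It then gives a between-arm comparison "presented as a difference in proportions and as an odds ratio from a logistic regression model adjusted for site and age". The sentence closes with one interval and one p-value: "adjusted for site and age, with a 95 % CI and *p*-value". A further sentence adds that "we will present the results as Number-Needed-to-Treat (NNT) and its 95 % CI". The Abstract has a shorter form: "primary outcome presented as differences in proportions and an odds ratio adjusted for site and age".

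Binary secondary outcomes follow the same pattern with site alone: "presented as a difference in proportions and as odds ratios from logistic regression adjusted for site".

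Three other places bear on this:
- Randomisation: an independent statistician "generated a randomization schedule using variable block sizes, stratified by site".
- Sample size estimation: the target is 60 % v 72 %, and the clinically important improvement is 12 %, so both are on the difference scale.
- Interim analysis and stopping rules: "the DSMB may recommend the trial be stopped if the level of significance of 0.001 is reached", with no test or effect measure named.

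**The concern.** A logistic model yields an odds ratio directly. It yields a difference in proportions only after a further step, such as averaging predicted risks, and the article states no such step. The adjustment phrase follows the odds ratio. The natural reading is that the difference and the NNT come from the raw two-by-two table while the odds ratio comes from a model with site and age.

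The scale on which the trial was designed, and which clinicians will use, would then take no account of the stratification by site. Two things are at stake. The first is some precision: an unadjusted standard error includes between-site and age variation that the design and model can remove. The second is clarity: close to the significance boundary the two presentations can point different ways, and the article does not say which one counts, either at the end or at the interim look.

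**Working it through.** **Inputs from the article.** 60 % v 72 %, two-sided α = 0.05, 80 % power, 244 per group, 1:1 allocation stratified by site, and 10 hospitals ("Study sites are 10 hospitals within the Australian and New Zealand PREDICT"). **Assumed, because the article gives neither:** the between-site SD and the effect of age per SD, both on the logit scale.

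**1. The plan's own figure.** Two-proportion formula with pooled variance under the null, mean proportion 0.66:

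n = [1.96·√(2·0.66·0.34) + 0.8416·√(0.60·0.40 + 0.72·0.28)]² / 0.12² = [1.313 + 0.559]² / 0.0144 ≈ 243.4, so 244 per group.

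This reproduces the stated figure, with power of 80.1 %. The trial is therefore sized for an unadjusted comparison. The planned effect equals an odds ratio of (0.72/0.28)/(0.60/0.40) = 1.71 and an NNT of 1/0.12 = 8.3.

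**2. Standard error of the unadjusted difference at the planned rates.** √[(0.60·0.40 + 0.72·0.28)/244] = √(0.4416/244) = 0.0425.

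**3. Simulation.** 488 children (2 × 244), 10 equal sites, 1:1 allocation balanced within site, complete data, 3000 trials per scenario. Three Wald tests are compared: the unadjusted difference, the log odds ratio adjusted for site and age, and the difference standardised from that same logistic model (delta method).

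| Site SD, age slope | Power: unadjusted / adjusted OR | Null rejection: unadjusted / adjusted OR | Unadjusted v OR disagree (planned effect) | Standardised v OR disagree (planned effect) |
|---|---|---|---|---|
| 0, 0 | 80.4 % / 80.9 % | 5.3 % / 5.6 % | 1.1 % | 0.3 % |
| 0.3, 0.2 | 81.1 % / 82.0 % | 5.2 % / 5.4 % | 2.0 % | 0.4 % |
| 0.5, 0.3 | 80.4 % / 82.2 % | 4.7 % / 5.7 % | 3.3 % | 0.5 % |
| 1.0, 0.5 | 81.8 % / 87.9 % | 3.7 % / 5.3 % | 6.8 % | 0.1 % |

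The Monte Carlo standard error of the 3.3 % is √(0.033·0.967/3000), or about 0.3 points.

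**4. The range used for the conclusion.** With site SD 0.3-0.8 and age slope 0.3-0.5, the standard error falls from about 0.042 unadjusted to 0.039-0.041 standardised, so the unadjusted one is roughly 3-8 % too large. Power rises by about 2-5 points with adjustment. The unadjusted difference and the adjusted odds ratio disagree at 0.05 in about 3-6 % of trials.

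**5. Error rate.** Under the null the unadjusted test rejects in 5.3 % of trials, falling to 3.7 % as site and age effects grow. Counting a trial as positive if either test is significant gives 5.7-5.9 %.

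**The case against.** The strongest reply is that the article never calls the difference unadjusted. In the Abstract the modifier could cover both measures, and a model-based difference is not excluded. The single interval and p-value come straight after the adjusted model. On that reading there is only one p-value, the difference is descriptive, and no conflict can arise. Estimator and pooling details are also commonly left to an analysis plan, which is not shown. This stands as a limit: the unadjusted reading is the natural one but remains an inference. It does not remove the point, because the article sets out its primary comparison and ties the adjustment to one of the two measures.

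A reader might infer more than the documents support:
- **That the unadjusted interval is wider than the design allows.** It is not. The 244 per group comes from the unadjusted formula, and unadjusted power is 80-82 % in every scenario.
- **That ignoring site inflates false positives.** As site and age effects grow the unadjusted test becomes conservative, so the loss is precision.
- **That the repeat analyses with further covariates exist only as odds ratios, so a shift could be mistaken for confounding.** The odds ratio does move when a prognostic covariate is added to balanced arms. But the article says that the analysis will be repeated, without limiting this to odds ratios, and nowhere says that a shift will be read as confounding.
- **That the difference must become the only primary measure, or that age must enter the secondary models.** Both are preferences. The article's choices there are acceptable.

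**Conclusion.** The point holds in a limited form. As naturally read, the primary difference and NNT ignore the site stratification and the age adjustment already specified for the odds ratio, and no test is named as deciding at the final or interim analysis. The unadjusted difference is valid and adequately powered.

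The cost is modest: a standard error about 3-8 % larger than needed, and a conflict with the adjusted odds ratio at p<0.05 in about 3-6 % of trials if both are tested. With no site or age effect that conflict falls to about 1 %, and at site SD 1.0 with age slope 0.5 it reaches about 7 %. These sizes rest on assumed site and age effects, equal sites and complete data; the planned multiple imputation was not simulated. The change is worth making because it costs almost nothing, not because the primary result is at risk.

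**What to change.** In the Statistical analysis section:

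1. State that the risk difference, its 95 % CI and the NNT are obtained by standardisation (marginal predictions under each arm, averaged over all participants) from the same logistic model with site and age, pooled over the imputed data sets.
2. Name one test from this model as the deciding p-value, for the final analysis and for the 0.001 interim look. The test of the treatment coefficient and the test of the standardised difference are both suitable; under the planned effect they disagreed in at most 0.5 % of simulated trials.
3. Do the same for binary secondary outcomes, keeping their stated adjustment for site.

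The cost is wording and a few lines of code, with a calculation slightly less simple than a two-by-two difference. No new data are needed and the sample size stays at 244 per group before loss to follow-up.
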